### Intervention

2.8

Licensed acupuncturists with at least 5 years of clinical experience will receive standardized training before trial initiation. Both groups will receive the same conventional acupuncture prescription: Sishencong (EX-HN1), Anmian (EX-HN22, bilateral), Shenmen (HT7, bilateral), Sanyinjiao (SP6, bilateral), Shenmai (BL62, bilateral), and Zhaohai (KI6, bilateral). Detailed acupoint locations are shown in Table 2 and Figure 2. Treatment will include 12 sessions over 4 weeks, three sessions per week. In the treatment group, ultrasound-guided SG acupuncture will be performed first, followed immediately by conventional acupuncture; after all needles have been inserted, needles will be retained concurrently for 30 min.

**Table 2 tab2:** Locations of selected acupoints.

Acupoint	Location
Sishencong (EX-HN1)	Located on the head, at four points situated 1 cun anterior, posterior, and lateral to Baihui (GV20).
Anmian (EX-HN22)	At the halfway point between Fengchi (GB20) and Yifeng (SJ17)
Shenmen (HT7)	Located on the anterior wrist region, at the ulnar end of the transverse crease of the palm, on the radial side of the tendon of the flexor carpi ulnaris.
Shenmai (BL62)	Located in the ankle region, directly inferior to the prominence of the lateral malleolus, in the depression between the lower border of the lateral malleolus and the calcaneus.
Zhaohai (KI6)	Located in the ankle region, inferior to the prominence of the medial malleolus, in the depression along the lower border of the medial malleolus.
Sanyinjiao (SP6)	Located on the medial aspect of the lower leg, 3 cun superior to the prominence of the medial malleolus, posterior to the medial border of the tibia.

cun: proportional bone (skeletal) cun. Baihui (GV20): located on the head, 5 cun directly superior to the midpoint of the anterior hairline. Fengchi (GB20): located in the posterior cervical region, inferior to the occipital bone, in the depression between the upper portion of the sternocleidomastoid muscle and the upper portion of the trapezius muscle. Yifeng (SJ17): located in the neck region, posterior to the earlobe, in the depression anterior to the inferior aspect of the mastoid process.

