#### Control group

2.8.1

Participants in the control group will receive standardized conventional acupuncture. Sterile single-use needles (0.25 × 25 mm, Jiachen Acupuncture Instruments Co., Ltd., China) will be used at EX-HN1, EX-HN22, HT7, BL62, and KI6, whereas 0.25 × 40 mm (Jiachen Acupuncture Instruments Co., Ltd., China) filiform needles will be used at SP6. Needling depth and angle will be adjusted within a prespecified range according to the anatomical features of each point and the participant’s local tissue thickness. Specifically, EX-HN1 will be inserted obliquely at an angle of 15°–30° along the subgaleal plane, with a target depth of 15–20 mm. At EX-HN22, the needle will be inserted perpendicularly or slightly obliquely to a depth of 10–15 mm, taking care to avoid excessively deep anterior needling. HT7 will be needled perpendicularly to 8–12 mm. BL62 and KI6 will also be inserted perpendicularly, generally to a depth of 8–12 mm. For SP6, perpendicular insertion will be performed to a depth of 25–30 mm. For bilateral acupoints, the right side will be needled first, followed by the left side. After deqi is obtained, needles will be retained for 30 min and removed, with brief compression using sterile gauze when needed.

Deqi will be elicited gently by lifting-thrusting and twirling manipulation after the intended depth is reached. Lifting-thrusting will use an amplitude of about 2–3 mm, and twirling will be kept within 90–180 degrees at approximately 1 Hz for 10 s. Manual stimulation will be applied after insertion and repeated at 10 and 20 min, giving each acupoint about 30 s of planned stimulation per session.

Deqi refers to the characteristic needling response induced by appropriate needle manipulation, including lifting-thrusting and rotation, after achievement of the intended insertion depth (37). Immediately after each manipulation, participants will rate typical needling sensations, including soreness, numbness, distension, heaviness, warmth, and radiating sensation, on a 0–10 numerical rating scale. At the same time, the acupuncturist will evaluate needle-grasp sensation, defined as the pulling, heaviness, tightness, or increased resistance perceived under the needle during manipulation, using a 0–3 scale. For the purpose of procedural standardization, Deqi will be regarded as achieved when at least one typical patient-reported sensation is rated ≥3 and/or the operator-rated needle-grasp score is ≥1 (38, 39).

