**Figure 3 fig3:**
[figure not shown]
Ultrasound-guided SG acupuncture. **(A)** Sonographic illustration of SG; **(B)** Ultrasound-guided acupuncture at the SG. SG, stellate ganglion; SCM, sternocleidomastoid muscle; IJV, internal jugular vein; CA, carotid artery; LCM, longus colli muscle.

Before each session, a safety checklist will identify bleeding tendency, anticoagulant use, recent neck trauma, cardiopulmonary instability, or other risk factors. Participants will be instructed to avoid swallowing, coughing, or neck movement during stepwise needle advancement. The procedure will stop immediately if severe pain, electric shock-like sensation, respiratory distress, or loss of continuous needle-tip visualization occurs. Local pressure will be applied after needle removal.

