### Assessment of safety

2.10

All adverse events (AEs) during intervention and follow-up will be recorded, including onset, duration, severity, management, outcome, and causality. AEs will be graded as mild, moderate, or severe. Mild AEs include transient symptoms requiring no specific treatment, such as local pain, minor ecchymosis, or transient dizziness. Moderate AEs include symptoms requiring clinical management or observation, such as persistent local pain, moderate hematoma, vasovagal reaction, transient hoarseness, dysphagia, or ipsilateral ocular symptoms. Severe AEs include marked functional impairment, hospitalization, or serious events such as suspected neurovascular injury, airway compromise, severe dyspnea, expanding cervical hematoma, pneumothorax, or loss of consciousness.

Common needle-related AEs, including minor bleeding and localized pain, will be managed according to standard clinical protocols. In cases of dizziness or needle syncope, the procedure will be immediately terminated; the participant will be placed in a supine position with continuous monitoring of vital signs and oxygen saturation (SpO2) until complete recovery. Supportive care will be provided as necessary, and participants with persistent symptoms will be referred to the emergency department for further evaluation. Specific attention will be given to AEs related to ultrasound-guided SG acupuncture, such as hoarseness, dysphagia, dyspnea, choking sensations, radiating paresthesia, and symptoms suggesting recurrent laryngeal nerve, phrenic nerve, vascular, or pleural involvement. Upon occurrence of these symptoms, needle manipulation will cease immediately, and the needle will be withdrawn under ultrasound guidance. Vital signs, airway patency, and neurological functions will be assessed immediately, with oxygen therapy administered if indicated. Participants exhibiting persistent complications (e.g., progressive neck swelling, suspected pneumothorax, or unstable vital signs) will be transferred to the emergency department and referred to appropriate specialists, including anesthesiology, otolaryngology, or vascular surgery.

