Vital signs will be measured before and after each treatment, and participants receiving SG acupuncture will be observed for at least 30 min. Serious AEs will be reported to the ethics committee within 24 h. Participants who discontinue or suspend components for safety reasons will continue to receive appropriate medical evaluation and will be encouraged to complete outcome follow-up whenever ethically and clinically appropriate.

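### Adverse events are looked for more closely in the stellate ganglion arm than in the control arm, so between-arm differences in mild or non-specific events may be inflated by unequal detection

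*Protocol article*

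**What the plan says.** Some of the safety collection in section 2.10 covers both arms. The general rule is "All adverse events (AEs) during intervention and follow-up will be recorded, including onset, duration, severity, management, outcome, and causality", with one mild/moderate/severe grading and no restriction by arm. Likewise "Vital signs will be measured before and after each treatment".

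Other elements are tied to the SG procedure:

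- The sentence that sets vital signs for everyone goes on to say that "participants receiving SG acupuncture will be observed for at least 30 min". No period is given for controls.
- "Specific attention will be given to AEs related to ultrasound-guided SG acupuncture, such as hoarseness, dysphagia, dyspnea, choking sensations, radiating paresthesia" introduces a list of symptoms to watch for. There is no corresponding list for conventional needling.
- The pre-session screen, "Before each session, a safety checklist will identify bleeding tendency, anticoagulant use, recent neck trauma, cardiopulmonary instability, or other risk factors", appears only in the description of the treatment-group procedure (section 2.8.2).

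Both arms have 12 sessions and the same conventional prescription (section 2.8). Needle retention is also the same length: "After deqi is obtained, needles will be retained for 30 min and removed" for controls, and "after all needles have been inserted, needles will be retained concurrently for 30 min" for the treatment group. Section 2.7 says that the acupuncturists cannot be blinded. Section 2.9 gives outcome assessment to a blinded clinician but does not say whether that includes asking about adverse events. Section 2.11 sets out no between-arm test of adverse events.

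**The concern.** The trial asks what SG needling adds to conventional acupuncture, and the Discussion reads any between-group difference as that add-on effect. The same logic applies to harm: the control arm is the only randomized reference for the harm that SG needling adds. That reference is sound only if an event of a given kind is about equally likely to be recorded in either arm.

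The conventional needling common to both arms can itself produce the events that section 2.10 grades as mild: local pain, minor ecchymosis and transient dizziness. These are the events whose recording depends most on whether someone is watching or asking. If one arm is watched for a set time with a symptom list in mind, by staff who know the allocation, and the other is not, part of any difference in such events may reflect detection. Grading may be affected too, because the moderate category in section 2.10 includes events that need observation. Control events never recorded cannot be recovered at analysis, and readers will compare counts by arm whether or not a test is planned.

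**Working it through.** The plan states no adverse event rate, detection probability or safety comparison, so there is no figure of its own to reproduce. The check has three parts.

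**1. What differs between the arms as written (protocol article)**

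| Element | Treatment | Control |
|---|---|---|
| All events recorded, common grading (2.10) | yes | yes |
| Vital signs before and after each treatment (2.10) | yes | yes |
| Sessions (2.8) | 12 | 12 |
| Needle retention (2.8, 2.8.1) | 30 min | 30 min |
| Minimum observation time (2.10) | at least 30 min | none stated |
| Named symptoms for special attention (2.10) | yes, for SG-related events | none stated |
| Pre-session safety checklist | in 2.8.2 | none stated |

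The restriction of the observation time to SG recipients is explicit. The restriction of the symptom attention is an inference, though a fair one, because the text ties it to events related to SG acupuncture.

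**2. How much extra observation**

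Section 2.10 does not say whether the 30 min starts after needle removal or overlaps the 30 min of retention.

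- If it follows removal at every session: 30 min × 12 = 360 min = 6 h per treatment-arm participant, and 6 h × 40 = 240 h over the arm, with no set period for controls.
- If it overlaps retention: the extra time may be nil, because controls also lie with needles in for 30 min. The difference in symptom attention remains.

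The contrast in time therefore runs from 0 to at least 6 h per participant, depending on the reading.

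**3. Size of the possible bias (assumed values, none from the documents)**

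Let π be the true risk of a mild event, equal in both arms, and let s_T and s_C be the detection probabilities.

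Observed risk = π × s. Apparent risk ratio = (π × s_T)/(π × s_C) = s_T/s_C.

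With π = 0.20 and 40 per arm, there are 0.20 × 40 = 8 true events per arm:

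- s_T = 0.90, s_C = 0.75: 8 × 0.90 = 7.2 against 8 × 0.75 = 6.0; ratio 1.2.
- s_T = 0.90, s_C = 0.50: 7.2 against 8 × 0.50 = 4.0; ratio 1.8.

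Over a wider grid, with π from 0.10 to 0.50 and 40 per arm, the last column is the chance that a two-sided Fisher exact test would give p < 0.05 with no true difference. The plan contains no such test; the column only gives a sense of scale.

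| s_T against s_C | Apparent ratio | Spurious risk difference | Fisher p < 0.05 |
|---|---|---|---|
| equal (1.00 each) | 1.00 | 0 | 1.7% to 3.3% |
| 1.00 against 0.90 | 1.11 | 1 to 5 points | 1.7% to 5.1% |
| 0.90 against 0.60 | 1.50 | 3 to 15 points | 2.1% to 21.2% |
| 1.00 against 0.50 | 2.00 | 5 to 25 points | 4.3% to 55.9% |

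The effect could be negligible or large, and nothing in the document narrows it.

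**The case against.** The strongest reply is that much of the safety collection is common to both arms. All events are recorded with the same attributes and grading, vital signs are taken around every treatment, and Table 1 schedules adverse events with no split by arm. Both arms attend three times a week, so bruising or lasting pain can be seen or reported at the next session. Staff return during retention to manipulate the conventional needles, and participants rate their sensations then. Closer watching after a riskier procedure is a safety measure, and any resulting bias runs against the experimental arm. No test of adverse events is planned, and a common elicitation form may exist in the full protocol, which is not shown.

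Most of this stands, and it limits the point. A reader might infer three stronger things that the document does not support:

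- **That every difference in adverse events is biased.** Hospitalization, pneumothorax or an expanding hematoma would surface in either arm. A difference in complications specific to SG needling would be largely real added risk.
- **That the treatment-arm watch is the only structured way of finding events.** General recording and vital signs apply to everyone.
- **That 6 h per participant, or 240 h, of extra observation is a figure of the plan.** It follows from only one reading of when the 30 min begins.

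The reply does not remove the core. The unequal observation is something the article states, not a detail it leaves out, and common recording of events does not make their detection equal. The absence of a planned test does not stop readers from comparing counts. A bias against the experimental arm still distorts the estimate of added harm.

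**Conclusion.** The point holds in a limited form. As written, section 2.10 gives the treatment arm a minimum observation time and targeted symptom attention with no stated counterpart for controls, in a trial where the treating staff are unblinded and both arms share needling that causes the same minor events. Between-arm differences in mild, transient or non-specific events may therefore be inflated in the treatment arm. Serious events and SG-specific complications are largely unaffected, and no planned inference is shown to be invalid.

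The size cannot be derived from the document. The ratios of 1.2 and 1.8 rest on assumed detection probabilities and on equal true risk in both arms. If a common elicitation form already exists in the full protocol, one sentence in section 2.10 saying so would settle the matter. The change is worth making before enrollment is complete because it is cheap and the lost information cannot be restored later.

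**What to change.** Leave the treatment-arm safety observation as the sponsor sets it. Add to section 2.10 one scripted adverse event checklist with the same wording and the same symptoms in both arms (hoarseness, dysphagia, dyspnea, choking, paresthesia, dizziness, local pain and bruising). Ask it at the same points: after needle removal, and before the next session or at the week 4 visit for the interval since.

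For reporting:

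- Use checklist events for the between-arm comparison of mild and non-specific events.
- Report all adverse events by arm alongside it, so that no harm found by direct observation is left out.
- Flag the events detected only during the treatment-arm observation.

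Basing the whole safety comparison on checklist events would be a mistake, since it could understate the harm of a new neck procedure; hence both presentations.

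The cost is about one minute of questions per session, one case report form page and a sentence or two in section 2.10, with no extra visits. Control-arm event counts may rise slightly.

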### Data analysis

2.11

All statistical analyses will be performed by an independent statistician using SPSS version 29.0 (IBM Corp., Armonk, NY, USA) and R software (version 4.3.x). The primary analysis will follow the intention-to-treat principle, including all randomized participants; per-protocol analysis will be used as sensitivity analysis. Continuous variables will be summarized as mean ± SD or median (IQR), and categorical variables as counts and percentages. Baseline characteristics will be summarized descriptively, with standardized mean differences used to assess group balance. No formal baseline hypothesis testing will be performed. Baseline fNIRS comparisons between patients with CID and healthy controls will use ANCOVA controlling for age, sex, BMI, caffeine/alcohol intake, and recording time.

Longitudinal continuous outcomes will be analyzed using linear mixed-effects models with fixed effects for group, time, and group-by-time interaction, and a random intercept for each participant. The main treatment effect will be the between-group difference in change from baseline to week 4; week 8 will be analyzed as follow-up. An unstructured covariance matrix will be attempted first; if convergence fails, AR(1) or compound symmetry structures will be considered based on model fit. Missing data will be handled under the missing-at-random assumption using multiple imputation by chained equations with 20 datasets. The imputation model will include treatment group, time, baseline and available follow-up values, and relevant variables such as age, sex, ISI, PSQI, and HAMA. Results will be pooled using Rubin’s rules.

This is a superiority trial. For ISI, the null hypothesis is no between-group difference in change from baseline to week 4; the alternative is greater improvement in the treatment group. A 3-point ISI difference will be used for sample-size estimation and clinical interpretation but not as a noninferiority or superiority margin. Because there are two primary endpoints, a two-sided Bonferroni-adjusted alpha of 0.025 will be used for each. Secondary outcomes and exploratory fNIRS endpoints will be adjusted using the false discovery rate method where appropriate.

Raw fNIRS data will be processed using NirMaster software (Znion, Wuhan, China). To ensure transparency and reproducibility, the data analysis pipeline will follow standard fNIRS processing procedures, structured into preprocessing, quality control, and feature extraction.

Data Preprocessing: First, the raw light intensity data will be converted to optical density (OD). Second, motion artifacts will be identified and corrected using spline interpolation. Third, a band-pass filter (0.01–0.1 Hz) will be applied to the OD data to reduce physiological noise (e.g., heartbeat, respiration) and low-frequency signal drift. Finally, the filtered OD data will be converted to relative concentration changes in oxy-Hb, deoxyhemoglobin (deoxy-Hb), and total hemoglobin (tHb) using the modified Beer–Lambert law. The differential pathlength factor (DPF) will be set to 6.0 for both 690 nm and 830 nm wavelengths.

Quality Control: Channel signal quality will be evaluated using the coefficient of variation (CV), which will be calculated based on the raw light intensity during the initial resting period. Channels with a CV > 15% will be considered to have excessive noise and will be excluded from further analyses (44). Participants with more than 20% of their channels categorized as low-quality will be entirely removed from the group-level fNIRS analysis.

Feature Extraction: In accordance with standard practices, oxy-Hb will serve as the primary indicator of cortical activation due to its higher sensitivity to task-related changes (45). To quantify task-evoked activation during the VFT, a GLM will be applied at the individual level. The design matrix will include the task conditions convoluted with a canonical hemodynamic response function (cHRF). Task-related regression coefficients (*β* values) will be extracted to represent the activation strength for each channel. For region-of-interest (ROI) analyses, the extracted *β* values from channels located within the bilateral dorsolateral prefrontal cortex (DLPFC) and medial prefrontal cortex (mPFC) will be averaged.

Longitudinal comparisons of ROI metrics (baseline, week 4, and week 8) will be conducted using independent-samples *t*-tests or Mann–Whitney *U* tests for comparisons between groups at each time point, with FDR correction applied to multiple fNIRS comparisons.

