### Participants

2.4

Patients with CID and healthy controls will be recruited through outpatient clinics and community channels, including WeChat and university campuses. Recruitment materials will describe the target population, eligibility criteria, intervention procedures, and contact details. Interested individuals will receive a study brochure and complete screening. Eligible patients will undergo baseline assessment and randomization, followed by assessments at baseline, week 4, and week 8. Healthy controls will undergo baseline clinical screening and baseline assessments before fNIRS acquisition.

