### Recruitment and procedure

2.5

Recruitment will take place at Tongde Hospital of Zhejiang Province Affiliated to Zhejiang Chinese Medical University through outpatient clinics and online notices distributed via WeChat. Recruitment materials will describe the target population, eligibility criteria, intervention procedures, and contact details. Interested individuals will receive a study brochure and complete a screening form. Eligible patients with CID will then undergo baseline assessment and randomization. Outcome assessments will be conducted at baseline, week 4 (post-treatment), and week 8 (follow-up). Healthy controls will be recruited as a reference group for baseline fNIRS comparison only. Before fNIRS assessment, their eligibility will be verified through clinical interview and baseline assessments.

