#### Eligibility criteria

2.6.2

Participants will be considered eligible for inclusion upon fulfillment of all of the following criteria:

Diagnosis of CID in accordance with the ICSD-3 diagnostic criteria, together with an ISI score of ≥10.Age between 18 and 70 years, with no sex-based restriction, and right-handedness.No use of medications or other therapeutic interventions for insomnia within 1 month prior to enrollment.Preserved ability for normal communication and compliance with study procedures.Written informed consent must be provided.

Healthy controls will be required to meet all of the following criteria:

Right-handed individuals of either sex, aged between 18 and 70 years;An ISI score ≤7, a Pittsburgh Sleep Quality Index (PSQI) score ≤5, and a HAMA score <7;No history of major chronic diseases or severe organic dysfunctions (e.g., cardiovascular, hepatic, or renal diseases);No use of hypnotics, antidepressants, central nervous system stimulants, or any other medications/substances known to substantially affect sleep architecture or central nervous system function within 1 month prior to enrollment;Voluntary provision of written informed consent prior to study participation.

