#### Exclusion criteria

2.6.3

Participants will be excluded upon fulfillment of any of the following criteria:

Presence of severe or unstable medical conditions, including cardiovascular or cerebrovascular disease, malignancy, nephritis, hematological disorders, other life-threatening diseases, or active infectious disease.Presence of severe depressive symptoms, defined as a Hamilton Depression Rating Scale (HAMD) score of >24.Presence of significant impairment in speech, language, or hearing, or the presence of cognitive or neurological disorders.Current substance abuse or severe dependence on alcohol or other psychoactive substances, or current exposure to medications or substances with substantial effects on sleep or central nervous system function, including antidepressants or central stimulants.Presence of secondary insomnia attributable to other organic diseases.Pregnancy or breastfeeding status.History of needle syncope or presence of skin damage at the intended acupuncture sites.Known allergy to metals, including acupuncture needles.Current participation in another clinical study.

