The present study is designed as a pragmatic add-on superiority trial in which both groups receive standardized conventional acupuncture, with the treatment group receiving additional ultrasound-guided SG acupuncture. Accordingly, any observed between-group difference reflects the add-on effect of SG acupuncture within this context, rather than the isolated effect of either modality. Several limitations warrant consideration. First, this is a single-center trial with a modest sample size, which may limit generalizability; furthermore, given the absence of published effect-size data for ultrasound-guided SG acupuncture in CID, the sample was powered to detect a clinically meaningful add-on difference in ISI, and smaller neurofunctional effects may be underpowered. Second, the absence of a sham SG acupuncture or para-needling control precludes determination of stellate-ganglion target specificity and prevents full separation of specific physiological effects from nonspecific needling, expectancy, therapist–participant interaction, or ultrasound-related contextual factors. Third, the short follow-up duration (final assessment at week 8) leaves the long-term durability of treatment effects uncertain. Fourth, fNIRS-derived Oxy-Hb signals reflect local cortical hemodynamics rather than direct neural activity, and are subject to confounding by systemic vascular status or CID-related neurovascular alterations; Oxy-Hb changes should therefore not be equated with neural activation or used to draw definitive causal inferences. Relatedly, the verbal fluency task engages prefrontal executive-linguistic networks specifically and may be influenced by semantic memory, linguistic proficiency, and educational background; task-evoked fNIRS responses should thus be interpreted as domain-specific rather than as a generalized index of executive function. Finally, as no universally accepted protocol for SG acupuncture currently exists, the manipulation parameters adopted here are protocol-defined, and optimal stimulation intensity, frequency, and treatment course remain undetermined.

Future research should employ multicenter, sham-controlled designs with larger samples, longer follow-up periods, and objective sleep measurements to confirm and extend these findings.

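### The baseline patient versus healthy-control fNIRS ANCOVA fixes its covariates without education, although the protocol says education may affect the task

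*Protocol article*

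**What the plan says.** The protocol article, Data analysis (2.11), gives the model for the non-randomized comparison in full: "Baseline fNIRS comparisons between patients with CID and healthy controls will use ANCOVA controlling for age, sex, BMI, caffeine/alcohol intake, and recording time". The list is explicit and not presented as examples.

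The limitations paragraph of the Discussion says of the verbal fluency task that it "may be influenced by semantic memory, linguistic proficiency, and educational background".

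On recruitment, Participants (2.4) says: "Patients with CID and healthy controls will be recruited through outpatient clinics and community channels, including WeChat and university campuses". Recruitment and procedure (2.5) describes recruitment "through outpatient clinics and online notices distributed via WeChat" and does not mention campuses.

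On anxiety, Eligibility criteria (2.6.2) requires of healthy controls: "An ISI score ≤7, a Pittsburgh Sleep Quality Index (PSQI) score ≤5, and a HAMA score <7". For patients the criterion is "Diagnosis of CID in accordance with the ICSD-3 diagnostic criteria, together with an ISI score of ≥10", with no HAMA limit. The only other mood-scale limit, in Exclusion criteria (2.6.3), concerns severe depressive symptoms, "defined as a Hamilton Depression Rating Scale (HAMD) score of >24".

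**The concern.** The Introduction makes characterizing brain function in CID one of the trial's aims, and the healthy controls are its only non-CID reference. They are a separate cohort, so randomization does not balance them against the patients. Whatever differs between the two groups, affects the task response and is not in the model can pass for a CID effect.

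Education is such a variable by the protocol's own account, and the covariate list leaves it out. Anxiety raises a related question: the entry criteria cap it in controls but not in patients, so the groups may differ in anxiety as well as in insomnia.

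What is at stake is how a baseline difference is attributed. The estimate of treatment effect is not involved.

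**Working it through.** **Comparison of the text**

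| Feature | Patients | Healthy controls |
|---|---|---|
| Education in the ANCOVA | no | no |
| Education matched or restricted in the article | not mentioned | not mentioned |
| Recruitment channels (2.4) | clinics, WeChat, campuses | the same |
| Age | 18–70, and a covariate | 18–70, and a covariate |
| HAMA limit | none | below 7 |

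The education gap and the HAMA asymmetry are both in the text. A difference in recruitment source between the groups is not.

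**Size, as an illustration**

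The plan gives no figure to reproduce here, so the calculation shows only how much an omitted covariate could matter.

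Inputs from the document (Sample size calculation, 2.3):
- 80 randomized patients, all due a baseline fNIRS;
- 24 planned healthy controls.

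Inputs assumed, because the document gives none:
- *r*, the within-group correlation of education with the task beta: 0.2 to 0.4;
- *D*, the education imbalance in SD units: 0.3 to 0.8;
- one two-sided test at 5%, with no true CID effect.

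Formulas:
- spurious standardized difference: *d* = *r* × *D*;
- noncentrality: *d* × √(n₁n₂/(n₁+n₂)) = *d* × √(80×24/104) = *d* × 4.30;
- false-positive rate: the noncentral *t* probability (102 df) beyond the two-sided 5% limits.

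Three cases:
- *r* = 0.2, *D* = 0.3: *d* = 0.06, noncentrality 0.26, rate 5.8%;
- *r* = 0.3, *D* = 0.5: *d* = 0.15, noncentrality 0.64, rate 9.8%;
- *r* = 0.4, *D* = 0.8: *d* = 0.32, noncentrality 1.38, rate 27.5%.

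Full grid for 80 versus 24:

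| *r* | *D* = 0.3 | *D* = 0.5 | *D* = 0.8 |
|---|---|---|---|
| 0.2 | 5.8% | 7.1% | 10.5% |
| 0.3 | 6.7% | 9.8% | 17.5% |
| 0.4 | 8.0% | 13.6% | 27.5% |

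Section 2.3 also sets a minimum of 20 per group for the fNIRS analysis. With 20 versus 20, the three cases give 5.4%, 7.5% and 16.7%.

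The formula treats education as wholly unadjusted. The planned model already contains age and sex, so *D* should be read as the imbalance left after the listed covariates. If education enters the model, acts linearly and is measured without error, the rate returns to 5%.

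**The case against.** The strongest reply is that little of this is demonstrated. Several stronger readings are tempting, and the document does not support them:

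- **Controls come from campuses and patients from clinics, so controls are younger and better educated.** Section 2.4 names the same channels for both groups, section 2.5 omits campuses, and age is already a covariate. An education imbalance is a possibility without known direction.
- **Depressive symptoms are also capped differently.** The HAMD exclusion is written for participants in general, and controls have no separate HAMD limit. Only the HAMA limit is shown to differ.
- **Controls are unmatched.** The article mentions no matching, but a condensed article may leave control recruitment to the full protocol. The point therefore rests on the covariate list that the article does fix.
- **A CID difference should be claimed only if it holds in patients with HAMA below 7.** That subgroup is of unknown and possibly small size, so a null result there could reflect lost power. The Discussion notes that anxiety often accompanies insomnia, so it may be part of the condition, and low-HAMA patients may not represent CID.

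It is also fair to say that the Discussion already calls for cautious, domain-specific reading of the task responses, and that under the mildest assumptions the inflation (5.8% against 5%) is negligible.

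These objections narrow the point but leave its core. A caution about the task does not deal with imbalance between non-randomized groups, and the listed model leaves out a variable that the protocol itself names as relevant.

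**Conclusion.** The point holds in a narrow form. The baseline patient versus healthy-control ANCOVA has a stated covariate list without education, against the protocol's own remark about the task. If the groups differ in education, part of any fNIRS difference could be misread as related to CID. The 5.8% to 27.5% range for 80 versus 24 depends wholly on assumed values of *r* and *D*. It shows that the effect may be trivial or material, and says nothing about which applies.

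The HAMA asymmetry is real but limits interpretation only. It does not make the comparison invalid, since comparing a clinical population with healthy people is what a reference group is for.

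A reader might infer that the treatment comparison is compromised. It is not: the ISI and Oxy-Hb change endpoints compare randomized patients with each other, and the healthy controls play no part in them. The point is minor.

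**What to change.** - Record years of education for patients and healthy controls, and add it to the baseline ANCOVA in section 2.11. This costs one case-report-form item and one degree of freedom. The item can still be collected after enrolment. The change should be documented before database lock and unblinding, as section 2.12 provides for amendments.
- State that, because low HAMA is required of controls only, a patient-control difference cannot be separated from anxiety.
- Add a descriptive sensitivity analysis in patients with HAMA below 7, reporting the estimate and its confidence interval, without making the main conclusion depend on it. HAMA is already scheduled at baseline, so no new data are needed. The estimate may be imprecise if few patients qualify.
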